#### Missing values

Attrition and dropout rates will be reported in terms of frequencies and percentages and patterns of missing data will be analyzed and respective tables and illustrations provided. Multiple imputation on 100 sets using chained equations with models according to variables’ scale levels will be performed for all main analyses [61].

#### Sensitivity analysis

Results for unimputed data will be reported and results of models adjusted for age and gender. Per-protocol analysis including only those who completed the treatment as planned (at least 70 percent of sessions) will also be performed [62]. Considering the likelihood of missing not at random (MNAR) in mHealth studies, we will also use reference group based imputation for establishing the impact of differential attrition on study results assuming that participants who dropped out during the study behaved like control afterwards [63].

#### Subgroup analysis

We will conduct exploratory subgroup analyses by sex, age, and drug intake adherence. To explore heterogeneity of intervention effects by subgroup, we will include an interaction term between intervention assignment and subgroup in models, and statistical significance will be determined with Wald tests.

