### Sample size

The primary outcome is the improvement of modifiable unhealthy lifestyles, with a reduction by at least one unhealthy lifestyle at 6 months considered a favorable outcome (coded 1) and any other outcome unfavorable (coded 0). According to a previous study, the prevalence of at least one unhealthy lifestyle in Chinese community residents is 89.6% [2, 37]. According to an analysis of the previous two survey waves of the CMEC, it is expected that 2 percent of the control group participants will achieve a favorable outcome. We assume that a 10% percent increase of participants with favorable outcome in the intervention group (to 12% in total) constitutes a minimally important difference.

To achieve a power *of* 0.80 to obtain a statistically significant signal at α <  = 0.05 for p_1_ = 0.02 vs. p_2_ = 0.12 with a chi-squared test of independence, the sample size is estimated as 204 (102 per group). To account for participant attrition of estimated 20%, recruitment target is 128 participants per group, with a total sample of 256 participants for assessment and evaluation.

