### Data analysis

Data analyses will be performed using R version 4.2.1 for Windows. All data will be securely stored in an electronic database and accessible only to researchers who meet the criteria as provided in the research ethics approval document.

Descriptive statistics will be provided for the baseline sample. Categorical variables will be summarized in terms of frequencies and percentage, in total and by intervention group. Continues variables will be summarized as mean ± standard or median (interquartile range) in total and by intervention group.

All main analyses will be performed on intention to treat (ITT) basis. The primary outcome will be analyzed with mixed effects log-linear Poisson regression of any reduction of unhealthy lifestyles at six months (favorable outcome vs not) on intervention group as randomized at baseline [58]. In addition, the model will include a random intercept for subject nested in village and a fixed effect for town (as number of clusters not sufficient for variance estimation in the latter case). Treatment effect at six months (immediately after intervention) will be provided as relative risk ratio [59]. As regards secondary outcomes, reduction of unhealthy lifestyles (favorable outcome vs. not) at all timepoints will be simultaneously analyzed with longitudinal mixed effects log-linear Poisson regression on timepoint, and an interaction term of timepoint and intervention group, with random intercepts for subject nested in village and fixed effect for town as specified for the primary outcome. Other binary outcomes including smoking/drinking quitting, drug intake adherence, frailty will be analyzed in the same fashion. For continuous outcomes including sleep quality, smoking/drinking carving, mental health outcomes, cognitive function, self-efficacy, implicit health attitude, social support, longitudinal analysis of covariance (ANCOVA) models with time and time-group interaction will be estimated, adjusted for the respective outcome at baseline and featuring random intercepts for subject nested in village as well as a fixed effect for town [60]. Estimates of differences in changes in lifestyles between groups at 3, 6, 9, and 12 months will be analyzed post hoc using Wald-tests.

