This study has the following limitations we are aware of at this point. First, although smartphones have a high coverage rate in China, some people (such as the elderly) may not be able to use them well, which may hinder the implementation and reduce the effectiveness of mHealth interventions. For example, the present study plans to use the apps WeChat and Tiktok as information resource transmission carrier, which may not be the most attractive tools for older people. However, offline interventions will include instructions on the use of these apps for promoting lifestyle changes. Second, for our primary outcome (lifestyles) and secondary outcomes (such as cognition), we mainly use questionnaire indicators, which may be subject to recall bias and socially desirable answer patterns. However, for some indicators prone to recall bias, we will provide documentation records for participants to help recall their lifestyles. Moreover, all group managers will receive standard investigation training (e.g., using sensitive and appropriate language when speaking about healthy lifestyles and chronic disease) and face to face offline investigation will be conducted in a private room. Third, due to the lack of balanced stratification, comparative analyses between subgroups may not be suitable if the sample size of each group is insufficient across groups (e.g., compare specific lifestyle factors across different types of chronic medical conditions).

Despite these limitations, the 3SLIFE trial presents an initial attempt at systematically promoting evidence-based community health promotion in China and is an important first step towards improved public health research, practice, and policy.

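### Minor: for the primary outcome, the Wald test of the arm-by-subgroup interaction in the log-linear model is unreliable at the planned 2% control rate

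*Protocol article*

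**What the plan says.** The Subgroup analysis section of the protocol article announces exploratory analyses by sex, age and drug intake adherence. The rule for heterogeneity is: "we will include an interaction term between intervention assignment and subgroup in models, and statistical significance will be determined with Wald tests". It does not say which outcomes this covers, how age or adherence will be categorised, or what happens when a cell has no events.

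The Data analysis section fixes the model for the primary outcome: "The primary outcome will be analyzed with mixed effects log-linear Poisson regression of any reduction of unhealthy lifestyles at six months". The effect is reported as a ratio of risks, with random intercepts and a fixed effect for town. No robust variance is mentioned, so model-based standard errors are the natural reading. The continuous outcomes are analysed by longitudinal ANCOVA.

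The Sample size section supplies the event rate: "it is expected that 2 percent of the control group participants will achieve a favorable outcome", against 12% in the intervention arm. On that basis, "with a chi-squared test of independence, the sample size is estimated as 204 (102 per group"), raised to 128 per group for 20% attrition.

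The limitations paragraph of the Discussion adds that "comparative analyses between subgroups may not be suitable if the sample size of each group is insufficient across groups".

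**The concern.** In a log-linear model the arm-by-subgroup term is the log of a ratio of two relative risks. It exists as a finite number only if all four arm-by-subgroup cells contain events. The plan's own control rate puts about one expected event in each control cell when an arm is split in two.

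If a control cell is empty, the estimate runs off to infinity and its model-based standard error grows faster still, so the Wald ratio goes to zero and p to 1. The test is then least significant where the observed contrast is greatest. The random intercepts and the town effect do not help, because the cell still holds no events. At stake is the only stated look at who benefits on the primary endpoint.

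**Working it through.** **Inputs from the protocol article.** Control 2%, intervention 12%, 102 evaluable and 128 recruited per arm (Sample size); log-linear Poisson model (Data analysis); Wald interaction test (Subgroup analysis). **Assumption, not in the document:** the share of each arm in the smaller subgroup, taken as 50% and varied to 20%.

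**1. The plan's own figure.** Pooled two-sided formula, mean rate 0.07:

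n = [1.96·√(2·0.07·0.93) + 0.8416·√(0.02·0.98 + 0.12·0.88)]² / 0.10² = (0.7072 + 0.2978)² / 0.01 = 101.01, rounded up to 102. Then 102 / 0.80 = 127.5, rounded up to 128. Both stated figures are reproduced.

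**2. Expected control events.** 0.02 × 102 = 2.04; 0.02 × 128 = 2.56.

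**3. Chance of an empty control cell.** P(at least one of two is empty) = 1 − (1 − 0.98^a)(1 − 0.98^b), with a and b the subgroup sizes.

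- 102 per arm, 51/51: 0.98^51 = 0.357; 1 − 0.643² = 0.586.
- 128 per arm, 64/64: 0.98^64 = 0.274; 1 − 0.726² = 0.474.
- 20/80 split: 73% (102 per arm) and 64% (128 per arm).

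**4. What the test returns then.** Example with 51 per cell: intervention 11/51 against control 0/51 in one sex, 1/51 against 2/51 in the other. A single-level Poisson fit gives an interaction of 23.5, model-based SE about 16,650, and Wald p = 0.999.

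Likelihood-ratio test on the same table: the event totals are 2 (control) and 12 (intervention) by arm, and 11 and 3 by sex, 14 in all. Without interaction, the expected counts are 2·11/14 = 1.571, 2·3/14 = 0.429, 12·11/14 = 9.429 and 12·3/14 = 2.571.

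G² = 2[0 + 2·ln(2/0.429) + 11·ln(11/9.429) + 1·ln(1/2.571)] = 2(3.081 + 1.696 − 0.944) ≈ 7.66 on 1 df, p = 0.006.

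A sandwich variance fails the other way. It gives a finite SE of about 1.2 beside a diverging estimate, so p is practically 0. It does the same for 6/51 against 0/51 and 6/51 against 2/51, where the treated arms do not differ at all.

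**5. Rejection rates.** 200,000 simulated trials per row, single-level, control 2% in both subgroups, model-based Wald with an empty cell counted as not significant:

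| Intervention rates in the two subgroups | Per cell | Wald | Likelihood ratio |
|---|---|---|---|
| 22% / 2% | 51 | 3.4% | 34% |
| 20% / 4% | 51 | 2.4% | 21% |
| 22% / 2% | 64 | 8.4% | 39% |
| 20% / 4% | 64 | 5.6% | 24% |
| 12% / 12% (no heterogeneity) | 51 | 0.1% | about 5% |

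With 20 villages of 5 men and 5 women and a village ICC of 0 to 0.05, Wald power at 22%/2% was 2.8% to 3.1%, so clustering does not change the picture for Wald.

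**6. When no cell is empty.** For control 1/51 and 1/51, intervention 10/51 and 2/51, the fit is finite: coefficient −1.61, SE 1.61, Wald p = 0.32, likelihood-ratio p = 0.33. The two tests then agree, and neither has much to work with.

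**The case against.** The case for leaving the text alone has real weight:

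- **Exploratory status.** The analyses are labelled exploratory and the Discussion already warns about subgroup size. This stands and keeps the point minor. The warning concerns numbers, however, and not a statistic that returns p near 1 on a table where another test of the same hypothesis gives 0.006.
- **Scope.** The rule refers to models in general. The ANCOVA outcomes are untouched, no 2% rate is stated for the other binary outcomes, and age could enter as a continuous variable. This stands.
- **Denominator.** Multiple imputation is planned for all main analyses. If the subgroup models follow, 128 per arm is the better figure, and imputed events may fill an empty cell in some sets. This stands: 47% is then the better guide, and even that ignores filled cells.
- **Detail for the analysis plan.** Sparse-cell handling could be left to a document not shown. That would excuse silence, but here the test is named.

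Stronger readings are tempting but are not supported. A reader might infer that the rule cannot work at all. Yet with two subgroups both control cells have events in 27% to 53% of trials over the splits examined, and the model can then usually be fitted. A reader might infer that real heterogeneity will be reported as absent; the article nowhere says a non-significant interaction will be read that way, and under a sandwich variance the error would run in the opposite direction. Nor does the problem force a move to risk differences, which test a different hypothesis from the planned relative risk.

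**Conclusion.** The point holds as a minor one, confined to the primary binary outcome with a categorical subgroup factor and model-based standard errors. There, at the planned 2% control rate, the named Wald test meets an empty control cell in about 47% to 59% of trials with two equal subgroups. It has about 3% power even when the whole effect sits in one sex (102 per arm), roughly a tenth of what a likelihood-ratio test achieves on the same scale.

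The size rests on the 2% rate and an assumed subgroup split. At a 10% control rate the chance of an empty control cell falls to about 1%. The likelihood-ratio figures ignore clustering, town effects and imputation. The deeper limit also remains: with 2 to 3 expected control events, the likelihood-ratio test reaches only about 21% to 39% power in the heterogeneity scenarios tabulated. A better test removes the perverse behaviour but does not make the subgroup question answerable with confidence.

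**What to change.** In the Subgroup analysis section, for the primary outcome:

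1. Replace the Wald interaction test with a likelihood-ratio or Firth-penalised test on the planned ratio scale. Adding a robust variance to the Wald test is not a remedy.
2. Show events and denominators for each arm-by-subgroup cell.
3. State that a non-significant interaction is not evidence of a uniform effect.

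The Wald rule can stay for the ANCOVA outcomes. A village-level risk-difference contrast may be added as a supplement if its scale is stated. Its power is attractive when the whole effect is in one sex (79% to 72% for ICC 0 to 0.05, with 5 men and 5 women in each of 20 villages), but at ICC 0 it falls to 57% at 20%/4% and 34% at 18%/6%. It also rejects about 25% of the time when the relative risk is a constant 6 and the control rates are 3% and 1%, where the planned scale has no heterogeneity.

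Cost: a few sentences and no new data. If the subgroup models use the imputed sets, a rule for pooling likelihood-ratio statistics across them must also be named.

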### Data monitoring

An independent academic supervisory committee of the CMEC will monitor the proper conduct of the trial and participant safety. During the RCT, participant’s interest will be overseen and safeguarded, the overall conduct of the trial will be monitored, and participants’ safety will be ensured by systematically checking negative events and reacting to any extreme distress. Additional help and counseling will be strongly recommended to participants in the case of any adverse event or emergency.

Periodical meetings will be held after each assessment point to ensure the proper progress of intervention and data collection.

Important protocol modifications will be communicated to relevant parties (i.e., supervisory committee, trial participants, trial registries, ethical committee, and researchers).

### Harms

An adverse event is defined as any unfavorable medical event that occurs after a subject has received an intervention, but is not necessarily related to the intervention. If the current state of the study subject is a pre-existing condition known from medical history, it should not be considered an adverse event unless there is a change in nature, severity, and association. Although the intervention is non-invasive, participants will be asked to inform research assistants as soon as they experience symptoms of discomfort. Any adverse events will be documented as to the nature of the event, time of occurrence, etc., and will be followed up until medically resolved. This study does not involve invasive manipulation or medication, and adverse events expected to occur may be related to the study participant's own illness or the trial. In the course of the trial, in the event of a serious adverse event, the first relevant treatment should be carried out immediately so that the impact of the adverse event on the study subject is minimized; if the interests of the patient conflict with the testing process, the interests of the patient are prioritized, and the trial is terminated if necessary. Study subjects may discontinue or withdraw from the trial at any time or report to the research team. Research assistant will keep a detailed record of all adverse events during the trial, including time, symptoms, and treatment, and report them to the Supervisory Group, the Ethics Committee, and the study sponsor.

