### Blinding

Those delivering interventions cannot be blinded to group allocation. Participants, assessors, and statisticians will be blinded throughout the entire trial period. Assessors are independent research assistants who are not involved in intervention delivery. Intervention providers are asked to not disclose group assignment to participants and assessors such as not talking about the mHealth intervention. Statisticians will receive data with unlabeled group coding and labels will only be revealed after completion of statistical analyses and start of interpretation of results.

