**Individual**		
Intervention	**·**Content: Providing medical consultation services and knowledge unrelated to healthy lifestyles (e.g., hospital treatment procedures) **·**Material: Homemade videos or weblinks to videos, and pictures **·**Provider: Group manager **·**Where: WeChat group **·**Schedule: For 6 months. Providing topics unrelated to healthy lifestyles twice a week	**Knowledge:** **·**Content: Providing medical consultation services and regular daily health knowledge related to healthy lifestyles and other topics (e.g., hospital treatment procedure) **·**Target: Changing misconceptions about healthy lifestyles; increasing knowledge about healthy lifestyles **·**Material: Homemade videos or weblinks to videos, and pictures **·**Provider: Group manager **·**Where: WeChat group **·**Schedule: For 6 months, providing topics related to healthy lifestyle once a day, and providing topics unrelated to healthy lifestyles twice a week **Skill:** **·**Content: One-on-one health coaching **·**Target: Guiding changes in unhealthy lifestyle; guiding engagement in healthy lifestyles; providing skills in maintaining healthy lifestyles **·**Materials: Live streaming platform, online course (e.g., exercise, diet), recipe (guided by the Mediterranean diet), tools (e.g., fitness aids such as elastic bands, medication aids) **·**Provider: Health professor, group manager **·**Where: WeChat and Tiktok live streaming platform, and homemade videos **·**Schedule: Being scheduled for 6 months. Live classes are offered twice a week; daily recipe and daily exercise guidance were provided
Self-management	None	**Empowerment:** **·**Content: Participants’ voluntarily online documentation of their daily lifestyle **·**Target: Self-management of health lifestyles with encouragement, self-supervision, and supervision from others **·**Materials: Gift (household goods) **·**Where: WeChat and offline activities **·**Provider: Group manager **·**Schedule: Inviting all participants document daily lifestyles (scheduled for 12 months) One-to-one online communication once a week to remind unhealthy lifestyle modification or healthy lifestyle maintenance (within 6 months). Being awarded with gifts consisting of daily necessities (e.g., soap and laundry detergent) for participants who document lifestyles well for that month in monthly offline activity (within 6 months)

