**Community**		
Intervention	**·**Content: Holding community health activities unrelated to healthy lifestyles (e.g., infectious disease prevention); providing free medical consultations **·**Provider: Group manager and local medical workers **·**Where: Local medical centers **·**Schedule: For 6 months. Providing offline community activities once a month and offline free medical consultations each quarter.	**Mutual support** **·**Content: Holding online activities (e.g., healthy lifestyle knowledge quizzes) and offline activities related to healthy lifestyle and other topics **·**Target: Increasing interpersonal interaction among participants in the same groups; improving participants’ knowledge and skills of healthy lifestyles **·**Where: WeChat group, local medical centers **·**Materials: Health tools (e.g., fitness aids such as elastic bands, medication aids) **·**Provider: Group manager and local medical workers **·**Schedule: Being scheduled for 6 months. Providing online community activities once a week (healthy lifestyle knowledge quizzes), and providing offline community activities once a month **Environments** **·**Content: Creating a healthy environment **·**Target: Creating environment/atmosphere to motivate participants’ healthy lifestyles **·**Where: WeChat group, local medical centers **·**Materials: Health tools (e.g., fitness aids such as elastic bands, medication aids) **·**Provider: Group manager and local medical workers **·**Schedule: Providing tools and announcing the rules for documentation, rules for awarding prizes as soon as the intervention is underway

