### Quality control and quality assurance

All assessors will receive online training (videoconference) as regards the study protocol, including ethical norms and detailed instructions with respect to the evaluation process. Detailed description of assessment procedure will be provided in a standard operation manual. All group managers will receive unified training and learn about experimental and control group interventions before group assignment. Health professionals from local health community hospitals will help scheduling participants to take part in the program and resolve any issues that may arise during the implementation of the intervention.

During the intervention period, a monthly meeting will be held to review the current implementation of the program. Moreover, a series of forms will be designed to document implementation and monitor participants’ safety and compliance, including a form for participant risk grading, and a diary of participants’ adherence to the intervention, with which we will be able to identify individuals at risk and engage in timely activism to improve or enhance interventions.

Quality control (QC) for interviews using scales and questionnaires includes data quality control through inspectors, who will check for outliers and human error on the same day of data collection. QC for medical examination includes checking whether the measurement instruments were in good condition and inspecting whether the measurement was in accordance with standard operating procedures (SOPs). QC for clinical laboratory tests includes sending blind panels of samples to additional Third-Party Medical Laboratories for QC testing. As for QC for data entry, two independent assistants will check the data entered electronically against the trial record sheets. Any data identified as unqualified will be excluded from final analysis. All qualified data is stored on a dedicated data platform before analysis.

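### The Harms section describes only volunteered adverse-event reports while the intervention arm has more personal contact, so any by-arm count is open to differential ascertainment of unknown size

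*Protocol article*

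**What the plan says.** Protocol article, Harms: "participants will be asked to inform research assistants as soon as they experience symptoms of discomfort". The same section says "Research assistant will keep a detailed record of all adverse events during the trial" and sends the reports to the supervisory group, the ethics committee and the sponsor. It states no scheduled question and no recall window.

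Data monitoring says that "participants’ safety will be ensured by systematically checking negative events and reacting to any extreme distress", without an instrument, a schedule or a statement about arms. Quality control and quality assurance adds that "a series of forms will be designed to document implementation and monitor" safety and compliance, again without naming an arm.

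Table 1 sets the contact. In the individual-level self-management row the intervention arm has "One-to-one online communication once a week to remind unhealthy lifestyle modification or healthy lifestyle maintenance (within 6 months"), provided by the group manager. The control cell of that row says none. At community level the control arm also has regular contact: "Providing offline community activities once a month and offline free medical consultations each quarter". The intervention arm has monthly activities and quarterly consultations too.

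Both arms are interviewed face to face at baseline and at 3, 6, 9 and 12 months (Data collection and outcomes). On who interviews, Blinding says "Assessors are independent research assistants who are not involved in intervention delivery".

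**The concern.** Where an event enters the record only because a participant mentions it, the number recorded depends on how often the participant is prompted to talk about health, and to whom. Table 1 makes that differ between the arms for six months. If the extra contact brings out more reports, equal true harm would look like an excess in the intervention arm. A real excess, for instance of exercise-related complaints, could equally be put down to reporting. Either way, counts by arm would be hard to interpret for the committee that monitors safety and for readers of the results.

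There is also a gap within the text. One section promises systematic checks, and the section that describes collection gives only a participant-initiated route. The two can both be true, but as written the reader cannot tell what is done, when, or whether it is the same in both arms. Collection cannot be made symmetric after the fact.

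**Working it through.** **1. The plan's own figures.** The protocol gives no adverse-event rate or reporting rate, so there is no safety figure to reproduce. The sample size reproduces (102 per group for 2% versus 12%, two-sided 5%, 80% power; 102 / 0.80 = 127.5, so 128 per group). It has no bearing on this point, except that 128 per arm is used in step 4.

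**2. Scheduled personal contact in months 1 to 6 (Table 1, taking six months as 26 weeks).**

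| | Intervention | Control |
|---|---|---|
| Weekly one-to-one communication | 26 | 0 |
| Monthly offline activities | 6 | 6 |
| Quarterly consultations | 2 | 2 |
| Sum | 34 | 8 |
| With the 3 and 6 month interviews | 36 | 10 |

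The ratios are 34 / 8 = 4.25 and 36 / 10 = 3.6. Live classes twice a week and weekly quizzes (intervention) and group posts twice a week (control) are left out. This shows that contact differs by design. It does not measure how many events are reported, because nothing in the text makes the weekly contact a reporting route.

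**3. Who hears the report.** Harms sends reports to research assistants. Table 1 has the group manager make the weekly contact. Blinding keeps assessors, who are research assistants, apart from delivery. The bias therefore needs an extra step: the contact prompts the participant to report, or the manager passes the symptom on. The protocol does not say how symptoms mentioned to a manager are handled, so the step is neither established nor closed off.

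**4. Illustration on assumed values.** Let the true risk r be equal in both arms and let s be the share of events reported. The observed risk is r × s, and the apparent risk ratio is s(intervention) / s(control), whatever r is. Take s(control) = 0.50, r = 0.20 and 128 per arm, so controls report 128 × 0.20 × 0.50 = 12.8 events.

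| s(intervention) | Reported events | Apparent risk ratio | Chance of a false 5% signal of excess harm |
|---|---|---|---|
| 0.60 | 15.4 | 1.2 | 7% |
| 0.75 | 19.2 | 1.5 | 23% |
| 0.90 | 23.0 | 1.8 | 45% |

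The last column is Φ[(d − 1.96 × SE0) / SE1], where d is the difference in observed risks, SE0 the pooled and SE1 the unpooled standard error. For the last row: d = 0.18 − 0.10 = 0.08; SE0 = √(2 × 0.14 × 0.86 / 128) = 0.0434; SE1 = √((0.10 × 0.90 + 0.18 × 0.82) / 128) = 0.0431; the argument is about −0.12, giving 0.45. With equal reporting the nominal value in that direction is 2.5%. For r from 0.10 to 0.30 the chance runs from 5% to 9% in the first row and from 24% to 66% in the last. Clustering is ignored. The risk ratios merely restate the assumed reporting shares: they show sensitivity and are not an estimate for this trial.

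**5. Months 7 to 12.** Instructed intervention and the control programme both stop, so contact becomes more alike. Daily lifestyle documentation, in the intervention arm only, is scheduled for 12 months, so a smaller difference remains.

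**The case against.** The strongest reply is that this is a condensed article. The wording of adverse-event enquiries and the forms usually sit in the full protocol or an operations manual, and the article mentions both safety forms and a manual. The absence of a stated question is therefore weak evidence that none exists, and asking participants to report promptly does not exclude systematic checks. This stands as far as it goes. It does not remove the point, because the article has a Harms section, that section names a route, and the route falls short of what Data monitoring promises.

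Second, controls are not left without contact. They have an assigned group manager and a local doctor or nurse, medical consultation services in the group, monthly activities, quarterly consultations, and the same interviews and physical and laboratory examinations. This stands and limits the bias.

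Third, the intervention is non-invasive and involves no medication, and no specified analysis depends on adverse-event counts. This also stands and keeps the point modest.

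Several stronger readings are tempting but unsupported:

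- A reader might infer that a planned harm comparison is confounded. The arms are randomised, so the mechanism is detection bias. Neither Harms nor Data analysis specifies a between-arm test of adverse events.
- A reader might infer that the safety forms cover only the intervention arm. The sentence names no arm, and controls receive their own programme over the same six months.
- A reader might take the 4:1 contact ratio as the size of the bias. It counts occasions for contact, not reports.

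**Conclusion.** The point holds as a modest weakness in how harms are collected. As written, the described route is volunteered report, the promised systematic checks have no procedure, and personal contact differs by arm for six months. Any by-arm tabulation of adverse events is therefore open to differential ascertainment. The likely direction is towards more recorded events in the intervention arm, on the assumption that more contact prompts more reports. The size cannot be derived from the document; the apparent risk ratios of 1.2 to 1.8 rest wholly on assumed reporting shares.

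A reader might conclude that the trial can make no valid safety statement at all. The text does not support that: the shared visits and the reporting line to research assistants could keep the difference small, and the full protocol may already contain a common enquiry. The primary outcome and the sample size do not depend on this point.

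**What to change.** Reconcile Data monitoring and Harms with one stated procedure:

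- At the 3, 6, 9 and 12 month interviews already planned, the blinded assessors ask every participant in both arms the same short, non-leading adverse-event question, covering the period since the last visit.
- The question comes after the lifestyle questionnaires, so that talk of symptoms or of the programme cannot colour the lifestyle answers or the assessor's blinding while those are being recorded.
- Any summary of harms by arm uses these solicited events.
- Spontaneous reports, and events that surface through intervention contacts, are still recorded for individual safety follow-up and are listed separately.

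If the full protocol already contains such an enquiry, a sentence in Harms saying so is enough. The cost is one short form, a few minutes of interview time at each of four visits, and some recall loss over three-month windows. The recall loss should be similar in both arms, which volunteered reports cannot be relied on to be.
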